The general visual protocol is adapted to the child’s age and developmental level and consists of exercises focused on the following functions: fixation, pursuit, visual attention, enhancing visual experiences and knowledge, perception of details and combining vision with motor action (visuomotor skills). The intervention program consists of several steps that can be applied to all functions:
Enhancing the diversity of training with different visual materialsEnhancing the duration of visual trainingDeveloping increasingly complex visual skills and behavior that are ecologically valid, i.e., related to the child’s activities and daily environment [20].

Visual input is provided in the form of different visual materials of different visual modalities (colors, black-white, moving and static objects, light and dark). The nature of visual input will be adapted to the preferences and abilities of the child, and successful responses and behavior will be rewarded (based on operant conditioning). Visual training of more complex skills and behavior is done by teaching the child to use a specific visual skill, to expand its use to other tasks and to integrate it in everyday life.

The supplement visual protocol is designed around the specific VPD that are determined based on results of the visual screening and assessments (VFA and observation) performed at baseline. For example, children with abnormal processing of form and motion information, but with normal processing of contrast and color information, will get additional training for the processing of form and motion-related visual information that is integrated within the visual intervention program itself in order to comprehensively support the child.

Additional components:
Focus moments. These therapy sessions with video feedback, evaluation with the parents and reports of behavioral observations, are done three times throughout the intervention period to determine whether the program suffices or needs adaptations.Stepping cards (per therapy session). An instruction for the daily practice sessions of parents that contains a specific goal, instruction, observational points, and evaluation.Logbook for therapists (per session) and parents (to be completed weekly). The logbooks are used to keep track of the frequency, intensity and content of the therapy sessions and the daily practice sessions by parents.Protocol for Activities & Materials to be used, based on chapter 5 [29]

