### Statistical analyses

#### Sample size calculation

To answer our primary research question about the effectiveness of early visual intervention programs on visual attention and processing functions in preterm children at risk of VPD, we use a repeated measures analysis of variance (ANOVA) for the parameter RTF as primary analysis. An a priori power analysis provided a recommended total sample size of 32 children (and an actual power of 0.81 and a critical F of 4.17).

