#### Effectiveness of visual intervention program

In children at risk of VPD who have been allocated to a visual intervention group, differences in viewing behavior parameter RTF between T0 and T1 are analyzed with a Repeated Measures ANOVA. A *p* value of 0.05 will be considered statistically significant. Covariates are the medical (perinatal and ophthalmic) and demographic factors and the repeated measures analyses will be done with and without them to obtain their contribution to the main effect. All analyses are done according to the intention-to-treat principle.

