#### Other effects of visual intervention on VPD (other parameters)

Secondary study parameters are the differences in other eye tracking-based parameters of viewing behavior and the outcomes of VFAs (e.g., visual acuity, contrast sensitivity, extent of visual field). Repeated measures ANOVAs with a *P* value of 0.05 will be considered statistically significant. After finding a main effect of group on the viewing behavior parameters, post-hoc comparisons will be done to establish which of the five visual stimuli significantly differ from each other in parameter values. For these comparisons, Bonferroni’s correction will be applied to the viewing behavior variables to correct the *P* value for the number of comparisons.

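### Holm's step-down should replace plain Bonferroni for the post-hoc comparisons over the five visual stimuli, and the comparison itself should be worded as direct versus postponed within each stimulus

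*Protocol article*

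**What the plan says.** The relevant text is in the protocol article, Statistical analyses, under the heading on other effects of visual intervention on VPD. Secondary parameters are analysed by repeated measures ANOVA at 0.05. The text then sets three things:

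- A precondition: "After finding a main effect of group on the viewing behavior parameters, post-hoc comparisons will be done".
- The aim of those comparisons: "to establish which of the five visual stimuli significantly differ from each other in parameter values".
- The multiplicity method: Bonferroni's "correction will be applied to the viewing behavior variables to correct the" P value for the number of comparisons.

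No reason is given for choosing Bonferroni, and no step-down alternative is mentioned.

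The primary analysis is separate. The Sample size calculation section under Statistical analyses names a repeated measures ANOVA "for the parameter RTF as primary analysis", and the next section says that "differences in viewing behavior parameter RTF between T0 and T1 are analyzed with a Repeated Measures ANOVA".

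**The concern.** Two features of this passage work against its purpose.

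First, plain Bonferroni holds every comparison to the strictest threshold, including those made after others have already been declared significant. Holm relaxes the threshold step by step as hypotheses are rejected, with the same guarantee on the family-wise error and no added assumption about correlation. A fixed choice of Bonferroni therefore loses power without buying error control.

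Second, the wording does not match the question. A comparison that follows a group effect should show on which stimuli the direct and postponed groups differ. Read literally, the text instead compares stimuli with one another, which says nothing direct about where the program works. It also leaves the number of comparisons open: five, or up to ten.

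At stake is the ability to say which visual functions improve. No false-positive risk is involved.

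**Working it through.** **Inputs from the article.** Five stimuli and alpha 0.05 (other effects on VPD). About 50 children at risk (the first Sample size calculation section), allocated half and half (Participant characteristics and timeline), so 50 / 2 = 25 per arm. The power statement gives a "recommended total sample size of 32 children (and an actual power of 0.81 and a critical F of 4.17", so 32 / 2 = 16 per arm as a lower case.

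**The plan's own figure.** F(0.95; 1, 30) = 4.171, which matches the stated critical F for two groups and 32 children. The power of 0.81 cannot be rebuilt because the article does not give the effect size, number of measurements or correlation. Nothing suggests it is wrong, and this point does not depend on it.

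**Inputs assumed, because the article gives none.** Normally distributed outcomes, equal correlation between stimuli, a two-sided t-test of direct versus postponed per stimulus, and a t-test on the five-stimulus mean at 0.05 to stand in for the overall group effect.

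**Thresholds.**
- Bonferroni, five tests: 0.05 / 5 = 0.010 for every test.
- Holm, ordered P values: 0.05 / 5 = 0.010; 0.05 / 4 = 0.0125; 0.05 / 3 = 0.0167; 0.05 / 2 = 0.025; 0.05 / 1 = 0.05. Testing stops at the first failure.
- If pairs of stimuli are meant: 5 × 4 / 2 = 10 comparisons. Bonferroni uses 0.05 / 10 = 0.005 throughout; Holm starts at 0.005 and relaxes from there.

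Holm's first threshold equals Bonferroni's and each later one is larger, so Holm rejects everything that Bonferroni rejects. When no stimulus responds, both make a first rejection in exactly the same trials.

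**Power when all five stimuli respond** (25 per arm, correlation 0.5, 0.8 SD, precondition kept, 20,000 simulated trials):

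| | Bonferroni | Holm |
|---|---|---|
| Average power per stimulus | about 56% | about 66% |
| All five detected | about 21% | about 45% |

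The differences are 66 − 56 = 10 and 45 − 21 = 24 percentage points. Here the overall test is significant in about 95% of trials, so the precondition costs almost nothing.

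**Power when few stimuli respond** (precondition kept):
- 0.8 SD on two stimuli, 25 per arm: at least one is detected in about 30% with either method.
- A larger assumed effect of 1.02 SD, 25 per arm, correlation 0.5: average power is 0.439 (Bonferroni) and 0.441 (Holm) with two affected, and 0.149 with either method when one is affected.
- 1.02 SD on one stimulus, 16 per arm: 0.106 with either method.

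**Family-wise error over the five tests when nothing works** (25 per arm, correlation 0.5): about 2.5% with the precondition, for either method; about 4.3% without it, again for either.

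**Joint error of the overall test plus the five comparisons when nothing works:**
- With the precondition, Bonferroni or Holm: about 5%.
- Without it: about 6.5–7% at correlation 0.5, and 5.8–7.9% over correlations 0.3 to 0.7. If the overall test were independent of the five: 1 − 0.95 × 0.95 = 9.75%.

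**The case against.** A reader might infer more: that the precondition and Bonferroni together are needless double protection, that Holm alone gives the same error control, and that deleting the precondition is free and would rescue stimulus-specific benefits. The apparent gain is large. With 0.8 SD on two of five stimuli, at least one is detected in about 30% of trials as planned and about 73% without the precondition. The documents do not support that reading, for four reasons.

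1. Equal error control holds only within the five comparisons. The precondition also holds the overall test and the comparisons together at about 5%, and that is lost without it. The article calls RTF a viewing behavior parameter, so the overall test may even be the primary one.
2. The jump from 30% to 73% has nothing to do with Holm. Without the precondition, Bonferroni also gives 73%; with it, Holm also gives 30%.
3. The 73% needs the same two stimuli to respond in every child. The intervention section does say that "children with abnormal processing of form and motion information, but with normal processing of contrast and color information, will get additional training", but that is a supplement fitted to each child's own deficits, on top of a general protocol identical for all. If each treated child gains 0.8 SD on a random two of the five, at least one detection occurs in 18% (plan) versus 21% (Holm without the precondition). A broad effect is at least as plausible, and then the precondition hardly matters.
4. The text speaks of stimuli differing from one another, so direct-versus-postponed tests within each stimulus are an interpretation until the wording is changed.

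It can also be said that the planned procedure is valid and conservative, and that only secondary post-hoc tests are touched. That stands and limits the weight of the point. It does not argue for Bonferroni over Holm, because Holm is at least as powerful under either reading of the comparisons and with or without the precondition.

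**Conclusion.** The point holds for the choice of Bonferroni and for the wording of the comparison. Holm's advantage in rejections is a mathematical fact and needs no assumption. Its size does: about 10 percentage points in average power and about 24 in detecting all five, under the assumed 25 per arm, correlation 0.5 and 0.8 SD on every stimulus. It is negligible if one or two stimuli respond. No effect size or correlation in the article supports or contradicts these values.

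The point does not extend to calling the precondition an error. Keeping or dropping it is a trade between joint error and power for selective effects. This is a modest gain in efficiency on secondary tests, worth taking because it costs almost nothing; validity and the primary RTF analysis are untouched.

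**What to change.** In the section on other effects of visual intervention on VPD:

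1. Word the post-hoc comparisons as direct versus postponed within each of the five stimuli, so that the family is five tests for the parameter concerned.
2. Replace Bonferroni with Holm over those five, with ordered thresholds 0.010, 0.0125, 0.0167, 0.025 and 0.05. If comparisons between pairs of stimuli are really intended, say so and apply Holm over those pairs.
3. Optionally, and as a separate decision, state whether the overall-effect precondition stays. Keeping it holds the joint error near 5%. Dropping it would help if benefit is confined to the same few stimuli across children, at a joint error of about 6.5–7% when nothing works, and that should be declared.

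The cost is a sentence or two of analysis wording, with no extra data, visits or children. Simultaneous confidence intervals are less simple under Holm; Bonferroni intervals can still be shown beside the Holm-adjusted P values. The change should be made before the follow-up results are analysed by group.

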#### Effects of visual intervention on neurodevelopment

At 2 years of age, parameters from Bayley-III-NL are used as indicators of neurocognitive development. First, the relation between the visual assessment parameters and Bayley-III-NL parameters of the cognitive composite score, the language composite score, and the motor composite score will be analyzed using Pearson and Spearman correlation analyses. Next, univariate ANOVA’s are used to analyze differences in Bayley-III-NL scores between preterm children without a risk of VPD and children at risk of VPD, and between preterm children at risk of VPD in the direct versus the postponed intervention group.

### Monitoring

#### Data monitoring and auditing

The risks of our study for patients and for scientific quality have both been judged as negligible, based on the NFU risk classification (Netherlands Federation of University Medical Centers). This risk level implies that monitoring should be done once a year. Monitoring involves:
Study documents and agreementsPatient inclusion, consent, compliance, and source document verificationPatient safetyStudy proceduresClinical data management systemCorrect saving of raw data, corrected data, and backups

#### Harms

In accordance with section 10, subsection 4 of the Wet Medisch-wetenschappelijk Onderzoek met mensen (WMO), the sponsor will suspend the study if there is sufficient ground that continuation of the study will jeopardize subject health or safety. The sponsor will notify the accredited Medical Ethical Testing Committee (METC) without undue delay of a temporary halt including the reason for such an action. The study will be suspended pending a further positive decision by the accredited METC. The investigator will take care that all subjects are kept informed.

### Ethics and dissemination

The present study has been approved by the METC of Erasmus Medical Center, Rotterdam (MEC-2016-724), on April 19, 2017. Important protocol modifications have been and will be communicated with the METC (in the form of amendments to the original protocol), project employees/researchers, and participating parents. Written informed consent will be obtained by the researchers before the baseline assessment, based on a comprehensive information document that the potential participants have received. See Additional file 2 for a model consent form.

Participant confidentiality will be protected through our data management policy (see section Data Management). The main investigator(s) and the participating medical and clinical specialists will have access to the final trial dataset. There are no contractual agreements that limit such access for investigators. During the course of the study, the principal investigator will have no access to patient-identifying data and communication will only be done using participant codes. The involved researchers and sponsors have no financial or other competing interests for the overall trial nor for each study site. No harm is expected from trial participation, in particular since most study components are part of standard clinical care. Therefore, ancillary and post-trial care are suspected to be non-applicable.

### Nature and extent of the burden, risks and benefits associated with participation

The risks associated with participation are negligible and the burden for the children is minimal. Apart from the visual assessment from 1 year CA onwards, the total program is standard care for children with (suspected) visual problems. Only the age at which this care is applied is advanced for this study, and the visual rehabilitation protocol has been structured in order to enable comparisons between children. There is a general burden for children to perform the study-specific assessments and for parents to accompany their children. A specific burden for parents of children in the intervention groups is the time and effort they are asked to invest in monitoring and logging the child’s daily practices in the home environment. Benefits for all preterm children are earlier visual assessments, general developmental support and, if applicable, earlier habilitation of a risk of VPD than is the case in conventional pediatric care (i.e., from 1 to 2 years CA instead of ~ 4 years CA).

### Dissemination policy

Dissemination of the results will include publications in peer-reviewed scientific journals and use of the visual assessments and the intervention protocol in clinical practice. There are no restrictions in the publication policy. The investigators aim to publish all results obtained from the study unreservedly.

### Authorship guidelines

Our study adheres to the Research Code of Erasmus MC in which guidelines for publishing and authorships are defined (https://www6.erasmusmc.nl/cs-research/bijlagen/publiceren?reason=404).

### Plans for granting public access to full protocol, dataset and statistical code

Public access to the full protocol will be given through this paper. All results will be published open access. The dataset will not be made publicly available given the patient identifying information it contains. Statistical code will be made available upon request.

## Discussion

The aim of this RCT is to investigate the effectiveness of an innovative and comprehensive visual intervention program for children with (a risk of) VPD from 1 year of age. We have developed a visual intervention protocol that adheres to recent scientific insights regarding habilitation and that exploits clinical expertise from visual rehabilitation centers in the Netherlands.

The present study provides a solution to some notorious problems in the (early) visual intervention domain. Firstly, an underlying problematic paradox in the execution of intervention studies is that the content of visual habilitation has to be tailored to the individual child in order to exert effects, but that establishing scientific evidence for effectiveness requires structured and controlled designs with homogeneous groups. With this protocol, we can achieve visual habilitation that is not only structured and evidence based, but also individually tailored and adaptive to a child’s level of functioning. Parts of the general visual protocol are currently used in visual practice but they have never been structured into one comprehensive protocol, and have never been the subject of scientific investigation. Since there is a lack of evidence-based visual intervention or training programs [20, 22], but clinical experiences are positive, these programs are considered best clinical practice. In addition, the supplement visual protocol and additional components were specifically designed for this study and satisfy the need for individually adaptive programs. Secondly, in order to obtain true evidence for the effects (does improvement occur as a result of the intervention or as result of ‘normal’ visual development?) an RCT is needed in which children with visual dysfunctions are randomly allocated to an intervention or control group. However, a difficulty with conducting RCTs in (young) patient groups is the ethical consideration regarding randomization of treatment allocation, which means that one group is withheld treatment. Our RCT design circumvents this problem. We start with providing intervention to all participants a couple of years earlier than is currently feasible within clinical visual care (from about 4 years of age). That way, both the intervention (from 1 year of age) and control group (from 2 years of age) will receive earlier care than usual and therefore are both expected to benefit from participation in this study.

This study has the potential to satisfy a great clinical and scientific need for early and evidence-based visual intervention options. To date, several reviews of visual interventions in children mentioned a lack of evidence-based programs. One showed some evidence for visual training as opposed to, more passive, visual stimulation [20]. Another focused on several strategies for visual improvement in children with frequently co-occurring visual and neurodevelopmental problems [22]. The strongest evidence was found for visual aids (e.g., spectacles) and environmental modification to compensate for visual loss. Less evidence was found for functional behavioral methods that focused on actually improving visual function, and it was stressed that more information on this subject is needed. Given the increasing prevalence of children with corrected low vision, i.e., for whom spectacles cannot provide more functional visual improvement, the availability of behavioral training programs is of the utmost importance.

It is important to note that the present study not only concerns early habilitation but also early screening of a VPD risk. A combined approach of detecting and habilitating VPD in children will benefit from the multidisciplinary collaboration of involved neuroscientists, neuropsychologists, and behavioral therapists. Upon achieving the study goals, this set-up also ensures immediate dissemination in the form of clinical implementation of the visual intervention program. The proposed training programs contain a unique combination of elements that ensures incorporation of a widely advocated system approach [38, 46]. This may not only improve VPD and their development, but also support the parent–infant relationship and improve infant self-regulation and later independence. Through the implementation of this new program, we expect that more children will gain opportunities for learning, development, and daily independence earlier in life. These are invaluable and essential steps toward an inclusive society that maximizes children’s opportunities.

The broader scope of this new intervention program lies in monitoring and supporting the development of children at risk, not only in the visual domain but also in behavioral, cognitive, and social-emotional domains. Focusing our attention on the early development of children born preterm will help set proper circumstances for further learning and development up to school age. Ultimately, we expect the outcomes to be applicable in all types of pediatric patients at risk of VPD (e.g., comorbid with syndromes or developmental disorders). The possibility to train visual functioning brings us closer to enhancing neurodevelopment in prevalent neurological risk groups and will optimize recovery or compensation on a functional and daily level.

### Study design challenges and limitations

An important challenge is to determine the right age to start interventions – how early is too early? This is yet unknown, which is why we chose to start at 1 year CA when basic visual and neurological development has completed and more developmental processes emerge. We expect that careful monitoring of visual assessment outcomes, not only related to interventions but also in the placebo control group and in the form of yearly follow-up measurements, will reveal the age(s) at which children start to show specific VPD. This will inform future clinical applications or new studies about the ideal developmental stages to start visual intervention programs. In addition, it was difficult to estimate the risk of VPD in this specific population of children born < 30 weeks at 1 year CA. The precise number will determine the inclusion and sample size of the intervention leg of the study. However, besides investigating effectiveness of visual intervention in children born preterm, the present protocol provides a solid basis for other studies and/or applications in different pediatric populations at risk of VPD early in life. Lastly, the study population is a relatively vulnerable risk group, particularly because of their young age. Children born very or extremely preterm generally go through a rough first start in the neonatal period, putting a medical and psychological burden on both the children and their parents. Therefore, we start recruiting at 1 year of CA when, for the majority of children, the most intense medical issues are behind them and caregivers may be open to exploring new developmental possibilities.

